### 2.2. Ethical Considerations

All participants will agree to participate with written informed consent. This study respects the ethical principles of the Declaration of Helsinki. The protocol for the study was approved by the Ethics Committee for Investigation with medicinal products of the Integrated Care Management of Albacete, Spain (5 October 2021, code 2021-094).

### 2.3. Sample Size

Participants will be recruited using a convenience sampling approach among eligible nursing students. After baseline assessment, participants will be randomly allocated to one of two parallel groups: (1) an intermittent hypoxia conditioning group or (2) a sham control group. The random allocation sequence will be generated using a computer-based random number generator with a 1:1 allocation ratio. To ensure balance between groups, block randomisation will be applied with variable block sizes. Allocation concealment will be guaranteed using sealed, opaque, and sequentially numbered envelopes prepared by an independent researcher not involved in participant recruitment or assessment.

The assignment of participants to study groups will be conducted by a researcher not involved in outcome assessment or data analysis. Due to the nature of the intervention, participants and intervention supervisors cannot be blinded to group allocation. However, outcome assessors and data analysts will be blinded to group allocation to minimise detection and analysis bias. Specifically, outcome assessors will evaluate CPR performance using anonymised, coded data with no group identifiers, ensuring that group allocation remains concealed. The randomisation sequence generation and allocation concealment will be performed by an independent researcher, who will have no involvement in outcome assessment or data analysis.

To control for potential confounding variables, a multivariate model (multiple linear regression) will be applied. The change in Q-CC following the intervention will be considered as the dependent variable, while potential confounders (e.g., age, sex, BMI, physical fitness, and blood parameters) will be included as covariates. Interactions between these variables and altitude conditions will also be explored.

The sample size calculation is based on an expected baseline proportion of correct compressions of 52%, according to a previous study [16]. Using Epidat 4.2 software, assuming paired comparisons, a 95% confidence level, and 80% statistical power, a total of 56 participants is required to detect an increase in the proportion of correct compressions to 78%. To account for potential dropouts or non-responses, the total sample size will be increased by 10%.

Given the need to assess specific physiological parameters, including ergospirometry and simulated high-altitude exposure, participants will be recruited based on feasibility. A balanced distribution by sex (approximately 50% per group) will be ensured.

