### 2.4. Interventions

#### Training CPR Programme

Participants without prior CPR training will undergo a standardised training programme designed in accordance with current European Resuscitation Council (ERC) guidelines. The training programme will consist of: (1) a theoretical session (60 min), including basic life support principles, recognition of cardiac arrest, and CPR sequence; (2) a practical hands-on training session (120 min), during which participants will practice chest compressions and ventilations using feedback-enabled mannequins under instructor supervision; and (3) a supervised skill consolidation session (30 min) focused on correcting technique and ensuring adherence to guideline criteria (compression depth, rate, recoil, and ventilation quality). The total training duration will therefore be approximately 3.5 h. Training will be delivered by certified instructors following a structured protocol to ensure standardisation across participants. Objective feedback devices will be used to facilitate motor skill acquisition and improve CPR quality performance. This training duration is consistent with previous literature demonstrating that structured sessions of at least 2–4 h are required for adequate acquisition of basic CPR skills and retention of performance quality.

Stage 1: An initial baseline assessment will be carried out in all participants (*n* = 56), consisting of collection of parentage data and anamnesis, as well as the measurement of physiological variables at rest (resting electrocardiogram and pulmonary function test), which will allow ruling out the existence of pathologies that contraindicate the performance of ergospirometry. Other measurements include diastolic blood pressure (DBP) and systolic blood pressure (SPB), anthropometry, ergospirometry to determine the maximal HR achieved and VO_2_max, muscle strength, and initial hypoxia tolerance test.

Stage 2: All participants (*n* = 56) will perform 10 uninterrupted minutes of CPR (with a CC/ventilation ratio of 30:2) on a mannequin with a quality measurement device for CTE and ventilations (Q-CPR) in the following situations:

Test M1: CPR at 670 m asl, FiO_2_ of 0.21.

Test M2: CPR at normal pressure simulating 3000 m asl, FiO_2_ of 0.14.

Test M3: CPR at normal pressure simulating 5000 m asl, FiO_2_ of 0.11.

Prior to M2 and M3, each participant will have an acclimatisation period of 10 min to FiO_2_ corresponding to each of the altitudes.

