To minimise the effect of fatigue between tests, each participant will have a 24 h rest period.

Stage 3: Participants assigned to the intervention group will undergo a standardised intermittent hypoxia conditioning programme (13 sessions, 45–75 min/session), including alternating cycles of hypoxia (FiO_2_ progressively reduced from 0.14 to 0.11) and normoxia, resulting in a total hypoxic exposure of approximately 728 min. The control group will undergo a sham protocol consisting of identical session structure and duration under normoxic conditions. Three to five weekly sessions will be held according to tolerance and the iAltitude^®^ protocol [42].

Stage 4: After the intervention, all the participants (*n* = 56) will perform three uninterrupted 10 min sessions of CPR: the first at 670 (P1), the second (P2) at 3000, and the third (P3) at 5000 m asl. To minimise the effect of fatigue between tests, each participant will have a 24 h rest period [42]. The criteria for completing the different CPR tests will be determined by reaching 10 min or by the physical and/or physiological limitations of the rescuer (physical exhaustion or pain, SatO_2_ < 75).

Throughout all stages, heart rate and peripheral oxygen saturation (SpO_2_) will be continuously monitored using an ear clip pulse oximeter. The training programme instructs the participant to breathe ambient air if the SpO2 level exceeds the limit specified in Table 1 (Lim SpO2). During hypoxia tests, as well as during conditioning, a nurse and/or a doctor with experience in emergency care will be present.

To minimise potential confounding due to independent practice, participants will be explicitly instructed not to perform any additional CPR training or practice outside the study protocol during the study period.

The pre-conditioning protocol for high-altitude exposure was designed based on experience and knowledge regarding the use of normobaric intermittent hypoxia (IHT) to enhance sporting performance. To this end, the following data were collected from each participant: age, sex, height, weight, body fat percentage, sport practised (if applicable), number of weekly training sessions, time spent training, and ability to perform CPR manoeuvres in accordance with the study design.

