SO_2_m: This will be measured with near-infrared spectrophotometry in biceps brachii and erector spinae. The data will be categorised into four phases: baseline, phase close to fatigue, the fatigue phase and the recovery phase—Humon Hex® (Humon Inc., Cambridge, MA, United States).

VO_2_max: Using ergospirometry, this will be categorised as very bad, bad, medium, good and very good level of cardiorespiratory fitness. It will be measured with a treadmill ergometer (HP-Cosmos, mod. Pulsar 3P) (h/p/cosmos sports & medical GmbH, Nussdorf-Traunstein, Germany), Cardinal Health electrocardiograph mod. Ergoline ER800 (ergoline GmbH, Bitz, Germany) and an automatic breathing gas analysis system (mod. Oxycom Alpha-Jaeger) (Erich Jaeger GmbH, Höchberg, Germany).

Cardiorespiratory fitness will be dichotomised as higher and lower using the Cooper Institute cut-off points for 20–30-year-old adults (VO_2_max ≥38 mL/kg/min for women and ≥43 mL/kg/min for men) [46].

Blood determinations: Before the start and after the completion of each test (pre and post) Hgb, Hct, Mb, and lactate levels in venous blood will be determined with Epoc^®^ Blood Analysis System devices (Siemens Healthineers, Ottawa, ON, Canada).

RPE: At the end of each of the CPR tests, the participants will be asked to rate the perception of the effort made using the Borg scale. It consists of numbers from 6 to 20, where each number represents a level of perceived exertion. The number 6 on the scale is associated with very light effort, whereas the number 20 is associated with maximum effort. The intermediate numbers on the scale represent increasing levels of perceived exertion [47].

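### Three allocation and masking statements do not fit the design: a sham arm with participants declared unblindable, an unclear time of allocation, and a sex balance promised without stratification

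*Protocol article*

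**What the plan says.** **Masking.** Section 2.4, Stage 3, describes the control condition: "The control group will undergo a sham protocol consisting of identical session structure and duration under normoxic conditions". Section 2.3 says: "Due to the nature of the intervention, participants and intervention supervisors cannot be blinded to group allocation". It adds that "outcome assessors and data analysts will be blinded to group allocation", working from coded data.

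**Time of allocation.** Section 2.3: "After baseline assessment, participants will be randomly allocated to one of two parallel groups". Section 2.4 uses nearly the same term for its first stage: "Stage 1: An initial baseline assessment will be carried out in all participants". Stage 1 contains anamnesis, resting physiology, anthropometry, ergospirometry, strength and a hypoxia tolerance test, but no CPR. The pre-conditioning CPR tests M1 to M3 are Stage 2. The opening paragraph of section 2 mentions CPR at the three altitudes, then random assignment, then CPR again.

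**Sex balance.** Section 2.3: "A balanced distribution by sex (approximately 50% per group) will be ensured". The allocation method in the same section is 1:1, and "block randomisation will be applied with variable block sizes". No stratification factor is named.

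**The concern.** A sham that matches the active sessions in structure and duration and differs in the gas breathed is normally chosen so that participants need not know their arm. Declaring them unblindable gives up most of that benefit.

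The outcomes make this matter. Ten minutes of CPR depends on effort, and a test may end early for exhaustion or pain. Perceived exertion is self-reported ("the participants will be asked to rate the perception of the effort made using the Borg scale"), as are state anxiety and the yes/no rating of one's own compressions and ventilations. A participant who knows that he or she was conditioned may try harder, or report less strain, with no physiological change. Coded data and blinded assessors come too late to correct this. Since the Discussion says that the study aims to demonstrate a benefit of conditioning, such an effect could pass for the result sought.

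The time of allocation matters for the same reason. If the arm were known before M1 to M3, the pre-test would be exposed too, and with it the change in Q-CC that section 2.3 models. Altitude intolerance, which section 2.1 makes an exclusion determined during simulated-altitude CPR, could then also be found after randomisation.

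The sex statement promises something that the stated method does not provide.

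**Working it through.** **1. Sham against unblinded participants (no arithmetic).**
- Stage 3 says what the arms share, session structure and duration, and what differs, hypoxia or normoxia.
- Section 2.3 attributes the lack of blinding to the nature of the intervention and says no more.
- Supervisors may need to know the gas setting. That does not by itself mean that the participant must.
- Outcomes that assessor blinding does not protect: effort during CPR and hence Q-CC, perceived exertion, STAI-SA, and self-perceived quality. All enter the between-group comparison of section 2.6 or secondary objective (e).

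**2. Order of events, side by side.**

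| Source | Implied time of allocation |
|---|---|
| Section 2.3, with the Stage 1 label in section 2.4 | after Stage 1, so before M1 to M3 |
| Section 2, opening paragraph | after the first CPR tests, before the repeat tests |
| Section 2.4, stage order | Stages 1 and 2 cover all participants; arms first appear in Stage 3 |

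The second and third rows favour allocation after M3. The first leaves the other order open.

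**3. Sex balance.** The plan gives no imbalance figure to reproduce. Inputs: 56 participants and a 1:1 ratio (section 2.3), so 28 per arm. Assumption: exactly 28 women are enrolled, which is the most favourable case for the promise.

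Blocks without a sex factor fix arm size but leave sex to chance. Ignoring the small effect of block structure, the number K of women in one arm is hypergeometric:

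P(K = k) = C(28, k) × C(28, 28 − k) / C(56, 28), with mean 14 and SD 1.89.

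| k | P(K = k) |
|---|---|
| 14 | 0.210 |
| 13 | 0.183 |
| 12 | 0.121 |
| 11 | 0.060 |
| 10 | 0.023 |
| 9 | 0.006 |
| 8 or fewer | 0.001 |

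- P(K ≤ 11) = 0.0905. By symmetry, P(11/17 or worse) = 2 × 0.0905 = 0.181. In such a trial one arm has at most 11/28 = 39% women and the other at least 17/28 = 61%.
- P(12/16 or worse) = 0.181 + 2 × 0.121 = 0.423. A 12/16 split is 43% against 57%.
- A simulation with blocks of 4 and 6 (assumed sizes) gives about 17% for an arm outside 40 to 60% women, close to the 18% above.
- With the 10% enlargement, 56 × 1.1 = 61.6, or 62. With 31 women and 31 per arm, the chance of an arm outside 40 to 60% is about 13%.

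With blocks of 4 and 6 run separately for 28 women and 28 men, an unfinished last block can leave a difference of at most 2 within each sex. The worst split of women is then 13/15, so each arm has about 46 to 54% women.

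**The case against.** **An open sham is not self-contradictory.** It still controls for time, attention and contact, and the plan states the lack of blinding openly. The text also suggests why masking is hard: every participant has a hypoxia tolerance test and performs CPR at FiO2 0.14 and 0.11 before conditioning, and the software alerts the user when the SpO2 limit is passed. This stands as a reason to expect imperfect masking. It does not show that masking must be given up. A reader might also infer that both arms use the same mask, device and display, but the article does not describe the sham equipment, so the point cannot rest on that.

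**The order of events favours the plan.** This largely stands. A reader might infer that participants know their arm before M1 to M3; the opening of section 2 and the stage order point the other way. What remains is a phrase that matches the wrong stage and needs reconciling.

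**The sex promise is only approximate, and sex is a covariate.** A 12/16 split arguably meets it, so the 42% figure should not be read as a failure rate; 18% is the fairer one. The regression in section 2.3 uses change in Q-CC, where a stable sex difference in level largely cancels, and adjusts for sex. The practical harm is therefore small, but adjustment afterwards does not ensure balance.

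**Reach.** The main aim is the within-person effect of altitude. Conditioning enters through secondary objective (e), and Q-CC is recorded by the mannequin software. That limits the masking point to the between-group comparison, although a device records performance and cannot tell effort from capacity.

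**Conclusion.** The point holds for three statements of unequal weight.

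1. The main one is the unexplained decision to leave participants unblinded in a sham-controlled comparison. It exposes effort-dependent CPR and the self-reported outcomes to expectation bias. The document gives nothing from which to size that bias.
2. The time of allocation is ambiguous, with the better reading being after M3. The passages must be reconciled.
3. Sex balance is not ensured by the stated method. Assuming 28 women among 56, the chance of an 11/17 split or worse is about 18%, or about 13% for the corresponding threshold with 62 enrolled. This is the least serious of the three.

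A reader might infer that the allocation as a whole is unprotected. The documents do not support that: the computer-generated sequence, its preparation by an independent researcher, sealed opaque numbered envelopes, and blinded assessors and analysts are all stated and are not in question.

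**What to change.** 1. **Masking.** Do not disclose the arm to participants until P3 is complete. Present both arms identically as far as the existing safety alerts allow, leaving those alerts exactly as they are. After P3, ask each participant to guess the arm and report the guesses by arm. If masking is still judged impossible, say why and list it among the limitations. Cost: protocol and consent wording and one extra question. Masking will be imperfect, because some participants will recognise hypoxia or receive alerts; the guesses show how far it held.
2. **Time of allocation.** Reconcile sections 2, 2.3 and 2.4 by stating that the envelope is opened only after M3. The pre-test is then unaffected by knowledge of the arm, and altitude-intolerance exclusions identified in M1 to M3 precede randomisation. Cost: one sentence.
3. **Sex.** Stratify the variable blocks by sex, with one envelope set for each. Sex is already a planned covariate and stays in the model. Cost: a second envelope set.

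The first two must be settled before participants reach allocation, and the third before the envelopes are prepared. Analysis cannot restore masking afterwards.

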There are numerous high-altitude regions around the world. Asia is home to the world’s highest point, Mount Everest in the Himalayas, at 8848 m above sea level (m asl). Around 400 million people worldwide live at altitudes above 1500 m asl [26,27], while around 140 million live permanently at altitudes between 2500 and 5500 m asl [28,29]. In addition, it is estimated that more than 100 million tourists visit mountainous areas around the world each year [30,31]. People’s interest in outdoor activities at high altitudes, such as hiking, mountaineering, skiing, and even following of these sports by amateurs, has increased considerably in recent years [32].

Being and moving at high altitudes produces various physiological effects, including an increase in cardiac and respiratory workload, especially during exercise [33,34]. Performing and maintaining quality CPR at high altitude could pose a significant physical challenge for rescuers. Preliminary studies have shown that, in resuscitators, after five minutes of CPR at altitude, arterial blood oxygen saturation (SaO_2_) decreases, and heart rate (HR) and the rating of perceived exertion (RPE) increase. This fact negatively affects the number of effective CCs, ultimately decreasing the quality of the CPR [27,28,29,30]. These variations have been studied by various authors at altitudes between 3100 and 3700 m asl [34,35,36,37,38,39].

Currently, it is not uncommon to find sports teams and supporters that exceed these altitudes during practice or monitoring. However, there are no studies analysing the quality of CPR performed at very high altitudes or how CPR results change after programmed conditioning at that altitude.

Normobaric intermittent hypoxia (NIH) involves breathing air with a low oxygen concentration at sea level. Its goal is to produce improvements typically associated with altitude acclimatisation, such as enhanced performance (increased oxygen transport, greater muscle efficiency and improved metabolic function), as well as haematological benefits (increased secretion of erythropoietin, haemoglobin and erythrocytes) [40]. However, haematological changes should be interpreted with caution, as it is likely that most protocols do not achieve the level of hypoxia required to induce meaningful erythropoiesis or lasting increases in haemoglobin mass [41].

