### 2.6. Statistical Analysis

First, a descriptive analysis of the study variables will be carried out, along with the appropriate tabulation and graphical representation of the data. Qualitative variables will be expressed as proportions with 95% confidence intervals, and quantitative variables will be described using means and standard deviations or medians and interquartile ranges, as appropriate. Prior to the application of parametric tests, the assumption of normality will be assessed for all continuous variables using the Shapiro–Wilk test.

For comparisons involving paired quantitative data, Student’s *t*-test for paired samples will be used when the normality assumption is met. If this assumption is violated, the non-parametric Wilcoxon signed-rank test will be applied.

For between-group comparisons (intervention vs. control), independent-sample t-tests will be used for normally distributed variables, while the Mann–Whitney U test will be used for non-normally distributed variables.

To evaluate the effect of the intervention across time and altitude conditions, a mixed-model ANOVA will be used, including group (intervention vs. control) as a between-subject factor and time (pre vs. post) and altitude as within-subject factors.

For categorical variables, McNemar or chi-square tests will be applied as appropriate.

A multivariate linear regression analysis will be performed to adjust for potential confounding variables (age, sex, BMI, and physical fitness), including group allocation as an independent variable. Model assumptions (normality, homoscedasticity, and independence of residuals) will be checked.

Statistical significance will be set at *p* < 0.05. All statistical analyses will be performed using IBM^®^ SPSS^®^ Statistics 28 software.

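### The adjusted regression for conditioning models raw change in Q-CC without baseline Q-CC, leaves the timing of blood covariates open, and adds altitude interactions that ordinary regression cannot handle correctly

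*Protocol article*

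**What the plan says.** The protocol article describes the adjusted analysis in two places.

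- **Section 2.3 (Sample Size).** To control confounding, "a multivariate model (multiple linear regression) will be applied". On the outcome: "The change in Q-CC following the intervention will be considered as the dependent variable". On the covariates: "while potential confounders (e.g., age, sex, BMI, physical fitness, and blood parameters) will be included as covariates". It adds: "Interactions between these variables and altitude conditions will also be explored".
- **Section 2.6 (Statistical Analysis).** A regression is planned "to adjust for potential confounding variables (age, sex, BMI, and physical fitness), including group allocation as an independent variable". The dependent variable is not named, blood parameters are absent, and independence of residuals is among the assumptions to be checked.

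Four other places bear on this.

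- Section 2.4 has every participant tested at all three altitudes before conditioning (M1 to M3) and again afterwards (P1 to P3).
- Section 2.5 has blood drawn before and after each test.
- The last paragraph of section 1 makes blood variation an outcome in objective (d). The same section counts among the goals of intermittent hypoxia "haematological benefits (increased secretion of erythropoietin, haemoglobin and erythrocytes".
- Section 2.6 also plans a mixed-model ANOVA with group between subjects and with time and altitude within subjects.

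**The concern.** Three features of the adjusted model matter for the estimate of the conditioning effect.

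1. **Baseline Q-CC is missing.** A change score fixes the slope of post on pre at 1. Estimating that slope is at least as efficient in large samples and uses data already collected. The mixed-model ANOVA does not recover the gain: with two time points and complete data, its group-by-time test is the change-score comparison averaged over altitudes.
2. **Blood parameters have no time limit.** Values from P1 to P3 come after the randomised intervention. Conditioning may change them, so they cannot confound the group effect. Lactate and myoglobin drawn after a test also follow the very CPR being scored. The two sections disagree on whether blood values belong in the model at all.
3. **Altitude enters an ordinary regression.** Altitude varies only within a person, so a covariate-by-altitude term cannot be estimated from one row per person. With several rows per person, a regression without a participant effect treats correlated rows as independent.

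At stake are the precision of the group effect, its interpretation if post-conditioning blood values enter, and the validity of its standard error if altitudes are stacked.

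**Working it through.** **The plan's own figure.** Section 2.3 gives N = 56 for 52% against 78%, paired, 95% confidence, 80% power. The McNemar formula is n = [1.96√ψ + 0.842√(ψ − d²)]²/d². Here d = 0.26 and, taking pre and post as independent because no discordance is given, ψ = 0.52×0.22 + 0.78×0.48 = 0.4888. This gives 54.3, so 55; the simpler form (1.96 + 0.842)²ψ/d² gives 56.8. The stated 56 is reproduced closely, and nothing below changes it. The document gives no pre-post or within-person correlation for Q-CC, so every correlation below is an assumption.

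**1. Change score against baseline adjustment.** Let pre and post have equal variance σ² and correlation r.

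- Variance of change: 2σ²(1 − r)
- Residual variance after baseline adjustment: σ²(1 − r²)
- Ratio: (1 + r)/2

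| r (assumed) | Variance ratio | Change-score SE larger by | 56 on change scores worth, with adjustment |
|---|---|---|---|
| 0.5 | 0.75 | 15% | 42 |
| 0.7 | 0.85 | 8% | 48 |
| 0.9 | 0.95 | 3% | 53 |

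The last column is 56(1 + r)/2.

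With unequal variances the saving is σ²_pre(1 − β)², where β is the slope of post on pre, so it shrinks as β nears 1. Example on altitude-averaged scores, with assumed SDs of 12 (stable person level), 8 (person-level change) and 8 (test-to-test):

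- σ²_pre = 144 + 64/3 = 165.3 and β = 144/165.3 = 0.87
- saving = 165.3×0.13² ≈ 2.8, against a change variance of 64 + 2×64/3 = 106.7, which is under 3%

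A simulation of that case showed no visible difference (SD of the group estimate 2.78 and 2.79). The gain is therefore real but ranges from useful to negligible.

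**2. Blood values.**

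| | Section 2.3 | Section 2.6 |
|---|---|---|
| Age, sex, BMI, fitness | yes | yes |
| Blood parameters | yes, timing open | no |
| Group | not named | yes |
| Baseline Q-CC | no | no |

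If a share m of a true effect Δ acts through a post-conditioning covariate, the adjusted estimate is Δ(1 − m), provided nothing else drives both covariate and outcome. For Δ = 10 points (illustrative) and m = 0, 25% and 50% this is 10, 7.5 and 5.0; simulation gave 9.95, 7.55 and 5.05.

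**3. Three rows per person in ordinary regression.** Let ρ be the correlation between one person's changes at different altitudes.

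- Group and other between-person terms: true variance is 1 + 2ρ times the reported variance.
- Covariate-by-altitude terms: reported SE is 1/√(1 − ρ) times the true SE.

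| ρ (assumed) | Group SE too small by factor | Type I error, group | Interaction SE too large by factor | Type I error, interaction |
|---|---|---|---|---|
| 0.2 | 1.18 | 9.8% | 1.12 | 2.8% |
| 0.5 | 1.41 | 16.6% | 1.41 | 0.6% |
| 0.8 | 1.61 | 22.4% | 2.24 | about 0% |

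Simulation with 56 participants and ρ = 0.33 gave 13.5% for group when stacked, 5.2% with one row per person, and 1.4% for an interaction term.

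**The case against.** The other side has a good deal.

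- **Change scores are valid.** Under randomisation they are unbiased, and the gain from adjusting depends on a correlation the document does not give. This stands: the point is about precision only.
- **Attenuation is not established.** Pre-conditioning blood values exist and could be the ones intended. The model in section 2.6 has no blood covariates. Section 1 itself cautions that most hypoxia protocols probably fall short of meaningful erythropoiesis, so the haemoglobin route may be small. A reader might infer that the plan will understate the effect; the documents support only that it could, if post-conditioning values are used and part of the effect runs through them.
- **Stacking is not stated.** A reader might infer that the plan produces falsely precise results. The data layout is not given, the interactions are exploratory, residual independence is to be checked, and the effect across time and altitude has its own repeated-measures analysis. For the interaction terms, stacking errs on the conservative side. What remains is that these interactions cannot be fitted without several rows per person, and the named method has no term for that.
- **Multiplicity and dichotomisation.** A reader might add that parallel tests of the group effect inflate error. Section 2.6 describes its tests by type of variable ("independent-sample t-tests will be used for normally distributed variables") and gives no list of tests on Q-CC from which to compute a rate. A reader might also object to cutting fitness in two: "Cardiorespiratory fitness will be dichotomised as higher and lower". Nothing says that this form enters the regression. Neither point is pursued.
- **The main aim is altitude.** Section 1 puts the effect of reduced oxygen fraction first and CPR quality after conditioning under objective (e). A model of post-conditioning scores alone must not displace that question. This is right and shapes the fix.

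**Conclusion.** The concern holds in three limited parts.

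1. Omitting baseline Q-CC is an avoidable loss of precision without bias: a variance ratio of 0.75 to 0.95 for r from 0.5 to 0.9 with equal variances, and almost no gain if the slope of post on pre is close to 1.
2. Sections 2.3 and 2.6 contradict each other on blood parameters, and section 2.3 leaves room for values measured after the intervention. The resulting attenuation equals the mediated share, which is unknown and may be small for haemoglobin.
3. If the covariate-by-altitude terms are fitted by ordinary regression on several rows per person, standard errors are wrong in both directions: too small for group and too large for the interactions. The size depends on an unstated within-person correlation.

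The documents do not show that the reported effect will be attenuated or falsely precise. They show a loosely fixed model that permits both. The sample size of 56 is not affected.

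**What to change.** - For the group comparison, add the Q-CC measured at the same altitude before conditioning (M1, M2 or M3) as a covariate.
- Replace the two covariate lists by one, used in both sections, that names group and is restricted to values measured before Stage 3. If blood parameters stay, name the draw; keep post-conditioning values as outcomes under objective (d).
- Where altitude enters the model, fit a linear mixed model with a participant random effect, or use cluster-robust standard errors. State this in place of multiple linear regression for those terms.
- Keep the within-person comparison of M1 to M3 as the analysis of the main aim, and say that the model above serves the conditioning question.

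The cost is analysis wording only. All variables are already collected, and neither the number of participants nor any procedure changes.
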